| STUDY DESIGN       | This is a randomised, controlled, double blind, parallel group, multi-country, Phase IIb study.                                                                                                                                                                                                                                                                                                                                                                                                                                                                                                                                                                                                                                                                                                                                                                                                                                                                                                                                                                                                                                                                                                                              |
| STUDY DIAGRAM      | 
The study diagram illustrates the flow of participants through three main study arms. It begins with 'Healthy Term infants' (n = 224) who are randomised into two formula arms: 'Test product: partially hydrolysed proteins' (n = 112) and 'Control product: intact proteins' (n = 112). A third arm, 'Full breastfeeding for at least 17 weeks' (n = 60 to 112), is also shown. The diagram tracks participants through 'Visit 1' (Screening and randomisation, age 0-14 days), 'Visit 2' (4 wk), 'Visit 3' (8 wk), 'Visit 4' (13 wk), 'Visit 5' (17 wk), and 'Call 1' (19 wk). It also indicates 'any feeding' status and 'any adverse events, concomitant medication or nutritional supplements and GI tolerability'. The number of evaluable infants (n*) is noted as 78 for each formula arm and 78 for the breastfeeding arm.
 
n* = number of evaluable infants
                                                                                                                                                                                                                                                                                                                                          |

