| 
OUTCOME
PARAMETERS
 
Primary
 
Secondary
(including
safety and
tolerance
parameters)
 | 
The primary outcome parameter in this study is weight gain in grams per day from baseline until 17 weeks of age.
 
Gain from baseline until 17 weeks of age of
 
 
• Recumbent length (mm/day)
 
• Head circumference (mm/day)
 
• Mid-upper arm circumference (mm/day)
 
 
Z-scores of anthropometric parameters at 17 weeks of age:
 
 
• Weight-for-age
 
• Weight-for-length
 
• Length-for-age
 
• Body Mass Index (BMI)-for-age
 
• Head circumference-for-age
 
• Mid-upper arm circumference-for-age as of 13 weeks of age
 
 
Blood parameters assessed at 17 weeks of age:
 
 
• Albumin
 
• Serum mineral markers: calcium, phosphorus, iron and magnesium
 
• Blood Urea Nitrogen (BUN; safety/adequacy)
 
 
These parameters will only be measured in blood of infants, whose parents gave additional consent to draw blood.
 
Safety parameters from baseline until 17 weeks of age as measured by:
 
 
• Number, type and severity of (Serious) Adverse events and possible relatedness to study product
 
• Use of (co-)medication
 
 
Gastrointestinal tolerance parameters from baseline until 17 weeks of age including:
 
 
• Occurrence and severity of gastrointestinal symptoms: 
 
- regurgitation (return of the milk into the mouth without force)
 
- vomiting (return of the milk into the mouth with force)
 
 
 
• Stool frequency
 
• Stool consistency
 
• Occurrence of diarrhoea
 
• Occurrence of constipation
 
 |

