| OTHER
PARAMETERS | 
Demographics of the infant:
 
 
• Number of infants from same pregnancy, including this infant
 
• Infant's age at enrolment
 
• Sex
 
• Race
 
 
Maternal and paternal medical and social characteristics:
 
 
• Age
 
• Self-reported Height
 
• Self-reported Weight
 
• BMI
 
• Relevant medical history
 
• Maternal alcohol use during pregnancy
 
• Maternal smoking habits during pregnancy
 
• Educational level
 
• First-degree relative with an allergy
 
• Allergy history parents and siblings
 
 
Medical information and other characteristics of the infant:
 
 
• Weight at birth
 
• Recumbent length at birth
 
• Head circumference at birth
 
• Gestational age
 
• Mode of delivery
 
• Apgar score at 1, 5, and 10 minutes after birth
 
• Medical history and prior use of medication between birth and enrolment
 
• History of defecation pattern and gastrointestinal tolerance symptoms during 3 days before enrolment (if applicable)
 
• Immunisation status
 
 
Feeding (history) characteristics:
 
 
• Duration of exclusive breastfeeding, derived from days between [days between birth and introduction formula/complementary feeding, whichever comes first]
 
• Age at introducing any commercial formula
 
• Age at onset of exclusively formula feeding
 
• Age at introducing study formula
 
• Age at fully formula feeding with study product, i.e. end of transition period from commercial formula to study formula
 
• Duration of mixed breast and formula feeding, derived from start and stop dates of breastfeeding and formula feeding
 
• Duration of exclusive formula feeding, derived from start of exclusively formula feeding and date end of study or date of introduction of weaning foods
 
• Use of feeding products, i.e., 
 
○ Name and type of the pre-randomisation provided commercially available products
 
○ Start and stop dates of study products
 
○ Type and start and stop date of complementary food or milk (to check compliance)
 
 
 
• Use of nutritional supplements
 
• Amount of study product intake in week before study visit (ml/day)
 
• Type of and age at introduction of weaning foods
 
 
In case of early termination:
 |

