| STUDY
PERIOD            | 
The duration of the study for each infant from enrolment to the final visit is 15-17 weeks, depending on the infant's age at study entry (max. 14 days).
                                                                                                                                                                                                                                                                                                                                                                                                                                                                                                                                                                                                                                                                                                                                                                                                                                                                                                                                                                                                                                                                                                                                                                                                                                                                                                                                                                                                                                                                                                                                                                                                                                                                                                                                                                                                                                                                                                                                                                                                                                                                                                                                                                                                                                                                                                                                                                                                                                                                                                                                                                                                                                                                                                                                                                                                                                                                                                                                                                                                                                                                                                                                                                                                                                                                   |

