| STUDY
DESCRIPTION       | 
After parent(s)/legal guardian(s) have agreed to and signed informed consent, infants may enrol in the study. Infants, whose mother has the intention to breastfeed her infant until the infants' age of 17 weeks, may be enrolled in the breastfeeding reference arm. Infants, whose mother has the intention to exclusively formula feed her infant as of 14 days of age at the latest, may be randomised to one of the infant formula arms. Infants will enrol in the study as soon as they pass the eligibility check (for more details see Error! Reference source not found. and Error! Reference source not found.).
 
At a maximum age of 14 days all infants will have a screening/randomisation visit (Visit 1), followed by four follow up visits when the infant is 4 (Visit 2), 8 (Visit 3), 13 (Visit 4) and 17 weeks of age (Visit 5). At the infants' age of 19 weeks the Investigator performs a phone call (PC) to parents of all participating infants to follow up e.g. on safety and outstanding issues, adverse events or transition to commercial product.
 
During the seven days before Visit 2, 3, 4 and 5, parent(s)/caretaker(s) of all infants are requested to fill out an eDiary on daily basis. The eDiary collects data on the intake of study products or breastfeeding, the infants' defecation pattern and aspects of gastro intestinal tolerance. Parent(s)/legal guardian(s) or caretaker(s) will receive automatic reminders from the eDiary system to fill out the diary.
 
Infants eligible for the infant formula arms
 
As soon as an infant is exclusively formula fed the screening/randomisation visit (Visit 1) takes place. At that time point, the infant will have a maximum age of 14 days.
 
After eligibility assessment, eligible infants will be randomised in a double-blinded manner to receive either the test product or the control product until the age of 17 weeks. This means that the infant receives the test or control product for a minimum duration of 15 weeks to a maximum duration of 17 weeks, depending on the age at randomisation. At Visit 1, the Investigator collects also baseline data on demographics, medical and social information, and anthropometrics. In addition, the Investigator provides the study product, gives instructions to the parents on how to use the eDiary and plans the next study visit.
 
At each of the following visits, the Investigator collects data on anthropometrics, study product intake, compliance with the study protocol, information on (Serious) Adverse Events, and information of use of medication and nutritional supplements. To support collection of data on intake of study product, the Investigator may use the data filled out by the parents in the eDiary. Likewise, data on gastro intestinal tolerance in the eDiary may support the assessment of e.g. Adverse Events related to gastro intestinal tolerance during the visits.
 
At visit 5, in addition to follow-up assessments a trained physician or nurse will draw a venous blood sample (1.4 mL) for assessment of plasma proteins and mineral status parameters, of infants whose parent(s)/legal guardian(s) provide informed consent for a blood sample on a voluntary base.
 
Infants eligible for the breastfeeding reference arm
 |

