|                      | 
As soon as parents or legal guardian(s) give informed consent, infants will have an eligibility assessment and enrol, if meeting the in- and exclusion criteria, in the study. The maximum age at enrolment is 14 days of age. These infants follow the same visit schedule and study assessments as the randomised infants as described above, including completion of the eDiaries and blood sampling (if separate informed consent for taking a blood sample is given).
 
 in case parents/caretakers cannot use eDiaries data will be collected via paper diaries
                                                                                                                                                                                                                                                                                                                                                                                                                                                                                                                                                                                                                                                                                                                                                                                                                                                                                                                                                                                                                                                                                                                                                                                                                                                                                                                                                                                                                                                                                                                                                           |

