| STATISTICAL ANALYSIS | 
The main statistical technique will be “repeated measurement” mixed models with randomised group as fixed factor. Sex and country are stratification factors used in the randomisation and therefore will be included in the models. Birth weight will be included as covariate in the primary model (i.e., the model on weight gain per day). The impact of factors that may influence the intervention effect may be evaluated by adding them as (time varying) covariates.
 
For concluding equivalence on the primary outcome parameter, the two-sided 90% confidence intervals for the differences in mean weight gain per day from baseline to 17 weeks of age will be calculated. Equivalence between the arms will be demonstrated at the 5% significance level, if the two-sided 90% confidence intervals for the differences in mean weight gain per day between the arms lies entirely between -3 g/day and +3 g/day. The margin of <math>\pm 3</math> g/day will be used if the pooled standard deviation (SD) of test and control group is equal or smaller than 6. If the pooled standard deviation is bigger than 6, an equivalence margin of <math>0.5 \times \text{SD}</math> will be used.
 
Equivalence in a secondary growth parameter is demonstrated at the 5% significance level if a two-sided 90% confidence interval for the difference in mean gain per day from baseline to 17 weeks of age between test and control lies entirely between <math>-0.5 \times \text{SD}</math> and <math>+0.5 \times \text{SD}</math>. SD is the pooled standard deviation of the gain per day (in growth parameter) from baseline anthropometric visit to 17 weeks of age computed from infants receiving test and control product.
 
Equivalence (at week 17) in a secondary z-score growth parameter is demonstrated at the 5% significance level if a two-sided 90% confidence interval for the difference in mean z-score between test and control lies entirely between -0.5 and +0.5.
 
The statistical analyses for the assessment of tolerance, safety parameters, blood parameters will be descriptive.
 |

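### Daily weight gain starts from a baseline at any age from 0 to 14 days, but age at that visit is not a committed model term; this costs little in the randomised comparison and could distort the breastfed one

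*Protocol*

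**What the plan says.** All references are to the protocol synopsis.

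- **Outcome parameters:** "The primary outcome parameter in this study is weight gain in grams per day from baseline until 17 weeks of age". The end of the interval is a fixed age.
- **Study diagram:** the start is Visit 1, labelled "Screening and randomisation, age 0-14 days".
- **Study period:** "The duration of the study for each infant from enrolment to the final visit is 15-17 weeks". The divisor of the daily gain therefore runs from 105 to 119 days.
- **Study description, formula arms:** "As soon as an infant is exclusively formula fed the screening/randomisation visit (Visit 1) takes place". Under the inclusion criteria this covers both infants whose mothers never intended to breastfeed and those whose mothers stopped within the first 14 days.
- **Study description, breastfeeding arm:** "As soon as parents or legal guardian(s) give informed consent, infants will have an eligibility assessment and enrol". No change of feeding has to happen first.
- **Other parameters:** "Infant's age at enrolment" is among the items collected.
- **Statistical analysis:** group, sex and country are in the models, and "Birth weight will be included as covariate in the primary model". Other factors may be added as covariates, but this is optional and none is named.
- **Study objectives:** equivalence of weight gain between the test formula and breast milk is a secondary objective. The breastfeeding arm is not randomised.

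**The concern.** Newborns usually lose weight and then regain it, so weight is not linear over the first two weeks. Depending on the day, Visit 1 may catch the birth weight, the lowest point, or a value already on the steady growth line. Gain per day then reflects the day of Visit 1 as well as feeding. Birth weight as a covariate cannot correct this, because it does not show where the infant stood on the loss-and-regain curve when the baseline was taken.

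The two comparisons are exposed differently. Age at Visit 1 is settled before allocation to test or control, so randomisation balances it on average. Nothing balances it between formula-fed and breastfed infants. Because the triggers for Visit 1 differ, mean age at baseline may differ too, and any such difference enters a comparison in which equivalence is to be claimed.

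**Working it through.** **Inputs from the protocol synopsis.** Visit 1 on day d, from 0 to 14; final visit at 17 weeks = 119 days; 78 evaluable infants per formula arm; margin ±3 g/day (0.5 × SD if the pooled SD exceeds 6).

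**Inputs assumed.** The synopsis gives no newborn growth figures. I take birth weight 3.4 kg, linear loss of 4-8% to day 3, linear regain to birth weight on day 8, 10 or 14, then 30 g/day. I use SD 6 because the margin rule turns on it; the synopsis states no planning SD.

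**Formula.** Endpoint(d) = (W17 − W(d)) / (119 − d), for the same infant with the same 17-week weight W17.

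**One worked curve (6% loss, regained on day 14).** W17 = 3400 + 30 × 105 = 6550 g.

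- Day 0: (6550 − 3400) / 119 = 26.5 g/day
- Day 3: (6550 − 3196) / 116 = 28.9 g/day
- Day 14: (6550 − 3400) / 105 = 30.0 g/day

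**All curves, same infant.**

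| Enrolment days | Spread of the endpoint (g/day) |
|---|---|
| 0-14 | 2.0-3.5 |
| 3-14 only | 0.05-1.7 |

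Most of the wide spread comes from days 0-2. In the worked curve, 2.4 of the 3.5 g/day arises between days 0 and 3.

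**Randomised comparison.** If enrolment is spread evenly over days 0-14, the added within-arm SD is 0.59-0.99 g/day.

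- Share of variance at SD 6: 0.59²/36 = 1.0% to 0.99²/36 = 2.7%.
- Standard error of a chance imbalance: 0.59 × √(2/78) = 0.09 to 0.99 × √(2/78) = 0.16 g/day.
- Half-width of the 90% interval at SD 6: 1.645 × 6 × √(2/78) = 1.58 g/day. Removing all of this variation would bring it to about 1.56-1.57.

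**Breastfed comparison.** The table gives the shift in the mean difference produced by enrolment day alone, as the later-enrolled group minus the earlier-enrolled group. The pairs of typical days are illustrations, since the synopsis does not give enrolment ages by arm.

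| Typical days (earlier, later) | Shift (g/day) |
|---|---|
| 0 and 10 | +2.0 to +3.3 |
| 2 and 8 | about 0 to +1.3 |
| 3 and 10 | −1.05 to +1.03 |

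**Effect of the estimator.** The synopsis names repeated-measurement mixed models but does not give the time axis. If a straight line were instead fitted through all five visits (4, 8, 13 and 17 weeks after Visit 1's day d), the same curves give a spread of 1.6-2.7 g/day over days 0-14 and 0.04-1.25 over days 3-14. The effect is smaller but of the same kind.

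**The case against.** The strongest reply is that the primary comparison is protected. Age at Visit 1 precedes randomisation, so it causes no bias in expectation, and the loss of precision is slight. That stands. A reader who sees a 2.0-3.5 g/day spread beside a 3 g/day margin might infer that the primary result is in danger. The protocol does not support that: the spread is an extreme contrast within one hypothetical infant, while the margin applies to a difference between arm means.

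A second reply is that bias in the breastfed comparison is conjecture. This stands in part. Both groups share the 14-day limit, infants never breastfed can qualify from birth, and no enrolment days by arm are given. One of the illustrations spans zero. A reader might infer from the different triggers that the comparison is certainly biased; they show only that it could be. Feeding choice confounds this comparison in any case, but that is no reason to leave a removable source of distortion.

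Third, the planned z-scores at 17 weeks are compared with breastfed infants and do not depend on the day of Visit 1. That also stands and limits the damage. It does not repair the daily-gain comparison, which is an objective in its own right.

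Fourth, a SAP may name the covariate, and the protocol already permits extra ones. But the endpoint, the triggers and the committed terms are fixed in the protocol, and the permission is optional and unspecific. A SAP that named the term would be carrying out the change proposed here.

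Finally, one might extend the point to gains in length, head circumference and arm circumference, which share the same start. The mechanism worked out here is newborn weight loss and regain, and no calculation supports that extension.

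**Conclusion.** The point holds in a limited form. Daily weight gain depends partly on when Visit 1 took place, and the protocol commits to no adjustment for that although the age is collected. For test versus control the consequence is a small loss of precision, about 1-3% of the variance at SD 6, and no bias in expectation. For test versus breastfed the consequence is a possible shift of unknown size and sign. It ranges from nothing to about 3 g/day in the illustrations, and only the extreme case, with one group measured around birth and the other around day 10, approaches or exceeds the margin.

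All the g/day figures rest on assumed growth curves, and the breastfed figures also on assumed enrolment days. What rests on the protocol alone is the variable start, the different triggers, the fixed end and the missing commitment to age at Visit 1.

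**What to change.** 1. Prespecify age at Visit 1 as a covariate in the weight-gain model, either as a non-linear term or in bands such as 0-3, 4-7 and 8-14 days.
2. For the breastfed comparison, also present gain from Visit 2 (4 weeks) to Visit 5 (17 weeks) beside the baseline-to-17-week figure.
3. Report the distribution of age at Visit 1 by arm, so that readers can judge whether the start of the interval differed.

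The cost is wording, a few degrees of freedom and one extra analysis; the age and the visit weights are already collected. The 4-to-17-week figure leaves out the first weeks of growth, so it should accompany the main figure and not replace it. If the arms barely overlap in age at Visit 1, the covariate will rest on extrapolation, and the 4-to-17-week figure will be the more reliable check.

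### The 17-week z-score models have no committed term for starting size, although the Visit 1 measurements that could supply one are collected

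*Protocol*

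**What the plan says.** The Statistical Analysis row of the synopsis names the method ("The main statistical technique will be “repeated measurement” mixed models with randomised group as fixed factor") and two terms common to all models ("Sex and country are stratification factors used in the randomisation and therefore will be included in the models"). It then adds one body-size covariate for one model: "Birth weight will be included as covariate in the primary model (i.e., the model on weight gain per day". A further sentence is permissive and names no variable: "The impact of factors that may influence the intervention effect may be evaluated by adding them as (time varying) covariates".

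Each secondary z-score has its own equivalence rule, met when the 90% confidence interval for the "difference in mean z-score between test and control lies entirely between -0.5 and +0.5". The Outcome Parameters row defines these z-scores as values at 17 weeks, whereas the primary and the other growth outcomes are gains from baseline. Arm-circumference z-scores are listed only from 13 weeks of age.

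The Study Description row confirms that starting values exist: "At Visit 1, the Investigator collects also baseline data on demographics, medical and social information, and anthropometrics". Infants in the breastfed reference arm follow the same schedule. The Study Objectives row lists z-score equivalence against breastfed infants as well as against control.

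**The concern.** A gain already subtracts the starting value; an attained z-score does not. Infants who are larger at Visit 1 will tend to be larger at 17 weeks, so part of the spread in the 17-week z-score reflects where each infant began. The two common covariates remove little of it: growth z-scores are normally standardised for sex, which leaves country.

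In the randomised comparison, the result is a wider interval than the data require and a 17-week difference that partly reflects chance imbalance in starting size. In the breastfed comparison, allocation is by feeding choice, so a difference in starting size need not be due to chance and could be read as an effect of feeding.

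**Working it through.** **Plan's own figure.** 78 evaluable per arm with 30% dropout: 78 / 0.70 = 111.4, rounded up to 112 per arm and 224 in total. This matches the Subjects row. Nothing below changes it.

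**Inputs.** From the synopsis: n = 78 per formula arm, margin ±0.5, two-sided 90% interval (z = 1.645). Assumed, because the synopsis gives neither: z-score SD 1, and correlation r between the Visit 1 and 17-week values, shown from 0 to 0.7.

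**Formulas.**
- Residual SD = √(1 − r²)
- SE = residual SD × √(2/78)
- Half-width = 1.645 × SE
- Power at true difference d = Φ((0.5 − d)/SE − 1.645) + Φ((0.5 + d)/SE − 1.645) − 1

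Unadjusted: SE = √(2/78) = 0.160 and half-width = 0.263. Power at d = 0 is 2Φ(3.12 − 1.645) − 1 = 0.86.

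| r | Residual SD | Half-width | Narrowing | Power, d = 0 | Power, d = 0.2 |
|---|---|---|---|---|---|
| 0 | 1.000 | 0.263 | – | 0.86 | 0.59 |
| 0.3 | 0.954 | 0.251 | 5% | 0.90 | 0.62 |
| 0.5 | 0.866 | 0.228 | 13% | 0.95 | 0.70 |
| 0.7 | 0.714 | 0.188 | 29% | 0.99 | 0.84 |

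**Chance imbalance.** Only r times the baseline difference carries through to week 17. At r = 0.5, an imbalance of one SE (0.160) contributes 0.08, and one of two SE contributes 0.16, about a third of the margin.

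**Effect of the entry limits.** Birth weight must lie between the 10th and 90th percentiles. As an illustration for the weight measures, suppose the starting z-score is a normal distribution cut at ±1.28 and does not spread again by Visit 1. Its SD is then about 0.66 (variance 0.44).
- An uncut correlation of 0.5 becomes 0.5 × 0.66 / √(0.75 + 0.25 × 0.44) = 0.36.
- The SE saving is 1 − √(1 − 0.36²), or about 7%, instead of 13%.

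**Gain models, for contrast.** Take SD 6 g/day (an assumption; 6 is the threshold at which the margin rule switches) and margin ±3. The unadjusted half-width is 1.58 and power 0.86. If the baseline value correlates with gain at 0.1, 0.2 or 0.3, the half-width becomes 1.57, 1.55 or 1.51 and power 0.865, 0.88 or 0.90. The narrowing is at most about 5%. For the primary, an assumed early weight curve gave about 2% of variance explained by adding Visit 1 weight and age, so the SE shrinks by 1 − √0.98, about 1%.

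**The case against.** The strongest reply is that secondary-model covariates are commonly settled in the statistical analysis plan, which is not at hand, and that the synopsis nowhere forbids a baseline term. That is fair, and a reader should not conclude that the z-scores will certainly be analysed without one. However, the synopsis does not leave covariates open: it lists them by model and ties birth weight to one model. On the text as it stands, no starting-size term is committed for the z-scores. The permissive sentence describes optional evaluation, not the estimate that decides equivalence.

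A second reply is that a repeated-measures model can carry Visit 1 as a response. It can, but this adjusts the week-17 contrast only if the arms are constrained to share a baseline mean. Without that constraint the contrast is essentially the unadjusted one, and the synopsis does not say which form is meant.

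Three stronger readings are tempting, and the document supports none of them:
- *Birth weight is the wrong covariate for the primary.* It is a legitimate pre-randomisation variable, and the outcome ("The primary outcome parameter in this study is weight gain in grams per day from baseline until 17 weeks of age") already subtracts the Visit 1 weight. Adding Visit 1 weight and age at enrolment would help little.
- *Only the primary model has a baseline covariate.* Sex and country are baseline covariates too. The gap concerns body size.
- *Chance imbalance decides equivalence, or the test is biased.* The unadjusted interval already allows for such imbalance, so the 5% level holds in the randomised comparison.

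The objection that the correlations are assumed, and that the entry limits probably lower them, stands in full.

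**Conclusion.** The point holds for the 17-week z-scores and is of low severity: a free improvement. No stated sample size, significance level or margin changes, and the primary conclusion is untouched.

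In the test-control comparison the benefit is precision: an interval about 5% to 13% narrower for correlations of 0.3 to 0.5, and possibly less under the entry limits on birth weight and head circumference. This rests on an SD of 1 and on 78 evaluable infants per arm. In the breastfed comparison, adjustment also reduces confounding by starting size, though it does not remove other differences between families who breastfeed and those who do not. The size of that effect cannot be computed from the document.

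For the primary and the other gain models, baseline terms are optional and of small benefit.

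**What to change.** State that each 17-week z-score model includes the Visit 1 z-score of the same measure as a covariate, alongside sex and country. If several visits are modelled jointly, let the covariate's coefficient differ by visit. For the arm-circumference z-score, which is listed only from 13 weeks, use raw arm circumference at Visit 1.

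Apply this to both the test-control and the breastfed comparisons. If Visit 1 is instead carried as a response with a common baseline mean, restrict that to the two randomised arms, since a shared mean is not justified for the breastfed arm.

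Optionally, add Visit 1 weight and age to the primary model and baseline values to the other gain models.

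The cost is a sentence in the protocol or the analysis plan, written before unblinding, and a degree of freedom per covariate term. The plan already schedules these measurements at Visit 1.
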